#### Data analysis: analysis of aims

Given the centrality of mediation and moderation in this proposal, we will use analytic methods based in SEM for RCTs [132]. We refer to our approach as a randomized explanatory trial (RET) because of its emphasis on the *explanation* of treatment effects on outcomes through mediation and moderation. The exogenous treatment condition is identified by a two-valued variable (0 = EDU, 1 = CBT). The endogenous outcome, our primary endpoint, is the CGI. Mediators are the primary transdiagnostic change mechanisms of the intervention. A powerful feature of RET analysis is that it pinpoints the specific facets where a program succeeds and where it falls short of eliciting mechanistic change that drives symptom relief. RET is not concerned so much with omnibus mediation effects but rather focuses on each link in a given mediational chain and identifies the link(s) where a chain is “broken” so that we learn what needs to be addressed technically to boost the therapeutic impact of CBT. See Fig. 2 for the RET schematic, which will be analyzed overall using SEM.

**Fig. 2 Fig2:**
[figure not shown]
Randomized experimental trial model of mediation analyses

Also of interest in an RET is the significance and magnitude of paths linking each mediator to the outcome. For example, perhaps a path associated with coping flexibility is not significant, suggesting that, contrary to our assumptions, coping flexibility does not meaningfully elicit UCPPS symptom improvement. In this case, we might consider streamlining the program so that it is simpler by eliminating the flexible problem solving. We will conduct state-of-the-art dominance analyses that allow us to order the relative strength of paths from the mediators to the outcome variable [133].

*Analyses for Aim 1:* Evaluate the efficacy of MC-CBT for UCPPS as compared to a nonspecific control intervention (EDU) in relieving pain and related symptoms. *H1a* states: Patients randomized to MC-CBT will show greater global symptom improvement on primary endpoint (CGI) compared to those randomized to EDU. This hypothesis will be tested using a covariate-adjusted single degree of freedom contrasts at each time point (immediate posttest 2 weeks, 3 and 6 months) comparing MC-CBT versus EDU on the full-scale CGI. Standard covariates will include medication history, gender, age, and indicators of symptom severity as measured at baseline. *H1b* states: MC-CBT will be superior to EDU on key secondary endpoints including the severity of pelvic pain and urinary symptoms, and functional impairment at post treatment. The same analytic strategy for H1a will be applied to secondary endpoints. For secondary outcomes, available baseline data will be included as a covariate.

*Analyses for Aim 2:* Evaluate the durability of MC-CBT relative to EDU at 3 months and 6 months following treatment discontinuation. This will be tested using the same approach as Aim 1 that is focused on the immediate posttest but now it will be focused on the time points of 3 months and 6 months, separately. The group differences in effects at one time point can be compared to the group difference at another time point using a single degree of freedom interaction contrast with time as a within-subject moderator, using a robust estimator (e.g., Huber-White or bootstrapping).

*Analyses for Aim 3:* Identify theoretically relevant change mechanisms that explain how and for whom transdiagnostically designed MC-CBT is more effective for the purpose of optimizing treatment effects. *H3a:* To evaluate the mediational dynamics that account for the precise cognitive processes that explain CBT’s effectiveness, we will focus on two types of analyses: (a) limited information estimation [134, 135] that focuses on selected mediational paths at a given time point (with exceptions noted below, where we introduce time lags), and (b) more complex mediational modeling using variants of full information SEM. For the former, we will first compare mean scores on each mediator for the MC-CBT versus EDU conditions using a robust single degree of freedom contrasts and using the baseline measure as a covariate and other covariates per Aim 1. These analyses provide limited information estimates of paths for each mediator at each time point. This between-group, ANCOVA-based framework is superior to more traditional mixed modeling strategies [136].

A second set of limited information estimation analyses will be performed that regress a given outcome (e.g., CGI) onto one or more variables from each of the transdiagnostic mediators as well as the treatment condition dummy variable and selected covariates (see Fig. 2). Importantly, given we will assess mediators at multiple time points during treatment as well as at the posttest and after, we also will be able to estimate effects of the mediator at time t-1 on the outcome at time t, thereby taking into account sequencing of time intervals. These analyses must be strategic and conducted relative to operative time dynamics.

*H3b: Trait self-regulation will moderate the impact of MC-CBT versus EDU on UCPPS symptom improvement both post treatment and at follow-up; those with higher baseline self-regulation will benefit more from MC-CBT than those with lower self-regulation.* This hypothesis posits the existence of moderated effects in the broader RET framework. A strength of RET analysis is that it can pinpoint where in the broader causal framework the moderated effect occurs. There are two loci where moderation might occur. First, low trait self-regulation might disrupt the effect of the treatment on the mediator; individuals low in self-regulation may lack the cognitive resources to complete the cognitive change tasks demanded of CBT and, as a result, the strength of path *from treatment to mediator* will be lower for low self-regulators than for high self-regulators. Another possibility is that those with low trait self-regulation cannot translate the skills they learn in coping skills training (e.g., flexible problem solving) to ease the burden of painful UCPPS symptoms, hence it disrupts the path *between moderator and outcome*. A powerful feature of RET analysis is that instead of merely identifying behavioral self-regulation as a treatment-outcome moderator, we identify where in the mediational chain it is impacting treatment effects. These tests will be executed using product term analyses with robust standard errors in SEM/regression contexts.

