### Participants and eligibility criteria

Planned enrollment is 240 adults between ages 18 and 70 (inclusive) of any gender, race, or ethnicity who have been formally assigned a diagnosis of IC/BPS or CP/CPPS (confirmed by a board-certified study urologist or urogynecologist) with clinically significant pelvic pain present for at least 6 months. Table 1 lists the inclusion and exclusion (urologic and general) criteria with corresponding rationales.

**Table 1 Tab1:** Participant inclusion and exclusion criteria

	Rationale

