#### Data analysis: statistical power analysis

The field has generally operationalized a clinically meaningful effect as a Cohen’s *d* of 0.50 or a correlation equivalent to it of 0.23, the latter of which represents about 5% explained variance [126–128]. Rather than framing power analysis as the probability of correctly rejecting a null hypothesis, we approach it in terms of effect size sensitivity. If a minimal clinically meaningful effect size is set at *d* = 0.50, it does not matter if we “miss” effect sizes less than *d* = 0.50 by failing to reject the null hypothesis for them because they are judged to be non-meaningful [129, 130].

Assuming conservatively a 12% failure to assess individuals, our final sample size of complete case data will be about 211 or about 105 per condition. For a traditional single degree of freedom contrast of means to evaluate paths from treatment to mediator and assuming a power of 0.80, the effect size sensitivity for a sample size of 100 per group is a population Cohen’s *d* of 0.39, which represents about 3.5% explained variance. This sensitivity will decrease somewhat if there is clustering, but the decrease will be offset by the use of baseline covariates. For a regression analysis to estimate paths from mediator to outcome with 8 predictors (to account for the simultaneous entry of mediators and covariates to control), and assuming a squared multiple correlation of 0.40, the effect size sensitivity for a given predictor will be the detection of a population coefficient that represents 3% unique explained variance. If we add a cluster adjustment representing an interclass correlation coefficient of 0.10, the sensitivity increases to 5% unique explained variance. These same statements apply for the analysis of moderation. The full information estimation structural equation model (SEM) we reference below will generally have equivalent if not greater statistical power than the above, so they, by definition, are adequately powered [131].

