One novel feature of EPPIC is our RET analytic approach for establishing whether the specific technical components that comprise transdiagnostic CBT for UCPPS work for the reasons previously hypothesized. RET allows us to unpack the specific strategies responsible for therapeutic benefit. If we isolate a specific therapeutic technique that impacts symptom relief by, for example, increasing cognitive flexibility, that strategy (e.g., flexible problem solving) can be isolated, accentuated, or amplified. Because symptom improvement is “time stamped” through repeated assessments in outcome and mediator when the corresponding module is introduced, clinical researchers may use information emerging from RET to re-sequence a particularly robust intervention if benefit occurs earlier than originally, thereby reducing dropout and maximizing patient satisfaction and benefit. If we find that a treatment module is relatively inert (i.e., introduction of a specific strategy does not correspond with a change in corresponding mediator or symptoms), then it can be abbreviated, modified, or jettisoned altogether. A microanalytic RET approach represents a major methodological innovation that can help engineer low-intensity treatments that are more efficient, less complex, and easier to disseminate and implement in routine clinical practice where uptake of evidence-based protocols is low.

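### A non-significant mediator-to-outcome path is read as showing that a treatment component does not matter; under the plan's own clustering allowance the trial cannot support that inference

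*Protocol article*

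**What the plan says.** All references are to the protocol article. In *Data analysis: analysis of aims*, the randomized explanatory trial (RET) approach is introduced as a search for weak points in each mediational chain: "RET is not concerned so much with omnibus mediation effects but rather focuses on each link". After Fig. 2 it continues: "Also of interest in an RET is the significance and magnitude of paths linking each mediator to the outcome". The worked example follows: "perhaps a path associated with coping flexibility is not significant, suggesting that, contrary to our assumptions, coping flexibility does not meaningfully elicit" symptom improvement, in which case "we might consider streamlining the program so that it is simpler by eliminating the flexible problem solving". The *Discussion* takes up the same theme. If introducing a strategy goes with no change in its mediator or in symptoms, the module counts as relatively inert, and "then it can be abbreviated, modified, or jettisoned altogether".

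The basis for reading non-rejection this way is in *Data analysis: statistical power analysis*. A meaningful effect is put at d = 0.50, "or a correlation equivalent to it of 0.23, the latter of which represents about 5% explained variance". Effects smaller than that may be missed "by failing to reject the null hypothesis for them because they are judged to be non-meaningful". The stated sensitivities at power 0.80 are d = 0.39 for treatment-to-mediator paths and 3% unique variance for mediator-to-outcome paths, or 5% with an intraclass correlation of 0.10. *Statistical methods* adds Holm adjustment, and clustering adjustment as needed. The article states no interval or equivalence criterion for calling a path absent.

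**The concern.** A non-significant test shows that an effect is negligible only if effects of the size that matters would rarely be missed. The example moves from non-significance to the absence of a meaningful effect, and on to dropping part of the programme. Magnitude is named alongside significance but has no threshold, and the example turns on significance alone. Aim 3 exists to optimise the treatment, so a false verdict of no effect could lead a later version of the programme to lose a working component. The question is whether the plan's sensitivity figures are good enough to carry the inference.

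**Working it through.** **Inputs.** "Planned enrollment is 240 adults between ages 18 and 70 (inclusive"), 12% loss, about 211 analysed or 105 per arm, 100 per group used for the d figure, power 0.80, 8 predictors, squared multiple correlation 0.40, meaningful effect d = 0.50 or about 5% variance. Assumed: two-sided alpha 0.05 (not stated); a Holm family of 4 (module-linked constructs in *Mediators*) or 6 (mediator instruments in Table 3); and that the plan's 5% applies to unique variance, the scale of its own sensitivity figure.

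**1. The plan's figures.** 240 × 0.88 = 211.2, as stated. Detectable d with 100 per group = (1.960 + 0.842) × √(2/100) = 0.396, against the stated 0.39; with 105 per group it is 0.387. For the regression path, f² = u/(1 − 0.40), where u is the unique variance, with noncentrality f²N on 1 and N − 9 degrees of freedom. The detectable u is 2.4% at N = 200 and 2.3% at N = 211, so the stated 3% is slightly conservative.

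**2. Mediator-to-outcome, no clustering.** At u = 5%, f² = 0.05/0.60 = 0.0833. With N = 211, the noncentrality is 17.6 and power is 0.987 (0.982 with N = 200). At the first Holm step with N = 211, power is 0.952 for 4 tests (alpha 0.0125) and 0.936 for 6 tests (alpha 0.0083).

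**3. Mediator-to-outcome, with the plan's clustering allowance.** Cluster size is not given, so the design effect is back-solved as the value that makes the stated 5% detectable at power 0.80: 2.10 (N = 200) to 2.22 (N = 211).

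| Alpha | Power at 5% unique variance | Missed |
|---|---|---|
| 0.05 | 0.80 | 20% |
| 0.05/4 | 0.62 | 38% |
| 0.05/6 | 0.56 | 44% |

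The last two rows are the worst case. Holm relaxes towards 0.05 as other paths are rejected, so the miss rate for a given path lies between 20% and these values.

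**4. What a just non-significant path excludes.** The standard error of the semi-partial correlation is about √(0.60 × D/(N − 9)), with D the design effect.
- N = 211, D = 1: SE 0.0545, estimate 1.97 × 0.0545 = 0.107, upper 95% limit 0.215, squared 4.6% (4.9% at N = 200). This just excludes 5%.
- N = 211, D = 2.22: SE 0.0812, estimate 0.160, upper limit 0.320, squared 10.2%. This does not exclude 5%.

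**5. Treatment-to-mediator at d = 0.50, 105 per arm.** Power is 0.950, so about 5% of such paths are missed. For six independent real paths, the chance of at least one miss is 1 − 0.9501⁶ = 0.264, about 26% unadjusted. Simulating Holm's step-down procedure for the same six paths gives 27%. With mediators correlated 0.5 (assumed), the Holm figure is about 20%. Baseline adjustment with an assumed correlation of 0.5 brings the independent-path 27% to about 8%. The 95% half-width without covariates is 1.96 × √(2/105) = 0.27, so a just non-significant d of 0.27 has an upper limit of 0.54, which does not exclude 0.50.

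**The case against.** The strongest reply is that the plan sets no rule. The passage is a hypothetical in tentative language, it names magnitude as well as significance, and a dominance analysis follows. The *Discussion* sentence does not mention significance and concerns later development of the programme. All of this stands, and a reader who infers a binding instruction to drop modules goes beyond the text. Dominance analysis, however, only orders the paths; it does not show that one is negligible.

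The second reply is that the power section supplies the missing argument: its sensitivities fall below the meaningful effect, so whatever is missed is unimportant. Simultaneous entry of mediators is already in the regression calculation, and results are to be compared with and without Holm. This also stands for mediator-to-outcome paths without clustering, and clustering is adjusted only as needed. It fails once the plan's own allowance applies, because the margin between detectable and meaningful disappears.

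A reader might also infer that the trial will very likely label a working component as inert. Taking power 0.80 for each of 6 or 12 independent links gives 1 − 0.80⁶ = 74% or 1 − 0.80¹² = 93%. But for treatment-to-mediator paths that power applies at d of about 0.39, which the plan calls non-meaningful. Likewise, 1 − 0.83⁶ = 67% applies alpha 0.05/6 to every path, which is Bonferroni. Holm gives 27% in that scenario. The documents do not support the stronger reading.

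**Conclusion.** The concern holds as a weakness in a stated inference, not as a faulty decision rule. Without clustering, non-significance on a mediator-to-outcome path comes close to excluding the plan's meaningful effect. With the plan's intraclass correlation of 0.10, it misses about one meaningful path in five before Holm and up to 38–44% at the first Holm step. For treatment-to-mediator paths the risk is small per path (about 5% at d = 0.50) and moderate across six (26–27%, less with baseline adjustment or correlated mediators), but a borderline non-significant result still leaves 0.50 inside the interval. These figures rest on two-sided alpha 0.05, a Holm family of 4 or 6, a design effect of about 2.15 back-solved from the stated 5%, and the plan's 5% read as unique variance. The primary efficacy analysis is unaffected.

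**What to change.** State in the analysis of Aim 3 that every path is reported with its 95% confidence interval, using the clustering adjustment actually applied. Call a link broken, inert or negligible only if the interval lies wholly below the plan's own meaningful effect: d = 0.50 for treatment-to-mediator, and about 5% unique variance for mediator-to-outcome (a semi-partial correlation of √0.05 = 0.224 in the expected direction). Call any other non-significant path inconclusive, and draw no conclusion from it about removing a component. Reword the coping-flexibility example and the *Discussion* sentence to match, before unblinding.

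The cost is wording only; no data or participants are added. The downside is that some paths will be reported as inconclusive. If the true treatment-to-mediator effect is zero, the upper limit falls below 0.50 about 95% of the time with 105 per arm. For a true zero mediator-to-outcome path under the clustering allowance, the criterion is met about 78% of the time, and about 19% of such paths would be inconclusive.

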### Interim analyses

Because of the safety profile of treatments, no interim analyses are planned.

### Oversight and monitoring

#### Data and safety monitoring

The EPPIC’s scientific integrity and safety will be monitored by an independent Data and Safety Monitoring Board (DSMB) composed of a urologist, biostatistician, and two behavioral scientists with subject matter expertise in chronic pain and transdiagnostic processes. The DSMB will meet annually. We will also appoint a Safety Officer who will serve as an independent evaluator (external to the study) of all adverse events (AEs), both serious and non-serious. In the case of this unmasked trial, the Safety Officer will work with the investigators to assure that any adverse event is fully documented. The Safety Officer will also review adverse event data to assess if the frequency of the AEs changes dramatically from baseline. Study-related adverse events will be reported to the NIDDK, Data Safety Monitoring Board (DSMB), and UB Institutional Review Board annually.

#### Consent and protection from risks

All participants deemed eligible will be consented during their baseline visit to the clinic. Consents will be conducted by a therapist or graduate research assistant. Each participant will be asked to sign the consent form and provided a copy. The consent form will provide an explanation of the purpose of the research, the expected duration of the individual’s participation, a description of the procedures, description of any reasonably foreseeable risks and benefits, a statement ensuring confidentiality and the voluntary nature of participation, information on compensation and intervention available, and information regarding who to contact for information on the research and their rights as a research participant. Risk reduction will include the preparation of a proactive policy for monitoring, assessing, and responding to suicide risk. During the acute phase, any participant showing significant deterioration or developing active suicidal potential as judged clinically by the treating therapist with confirmation of testing data will be removed from the structured protocol and triaged immediately to more intensive clinical intervention in the community. The policy is the product of a larger effort that emphasizes best practices for managing individuals at increased risk for suicide in clinical research setting by training and supervising staff to identify suicide risk in study patients, identifying community resources to respond to risk, and documenting and reporting suicidal behaviors.

### Adverse events and harms

Study-related adverse events will be reported to the NIDDK, EPPIC DSMB, and University at Buffalo Human Subjects Institutional Review Board (IRB) annually. Serious adverse events (death, life-threatening, new, serious, or permanent disability) that are determined to be related to the study procedures will be reported to the UB IRB within 72 h and will be reported to the NIDDK Program Officer within 7 days of incident. Other serious, unexpected, and treatment-related adverse events will be reported to the NIDDK Program Official within 15 days and to the UB IRB within ten business days. The proposed trial will be stopped only if the DSMB believes there is an unacceptable risk of serious adverse events attributable to one of the treatment arms. In this case, the DSMB could decide to terminate one of the arms of the trial or the entire trial.

#### Confidentiality

Confidentiality and the protection of protected health information will be ensured by following the Privacy Rule of the Health Insurance Portability and Accountability Act (HIPAA) guidelines and the regulatory guidelines for these issues as required by the UB Institutional Review Board. All study participants will be assigned a unique ID number that will be linked to their contact information through an encrypted and password-protected electronic file stored securely and separately from their research data. Digital files will be maintained in a computerized database housed on a username and password-protected fileserver. Hard copy and digital data will only be accessible by authorized study personnel formally trained in research ethics and compliance. All EPPIC personnel are required to complete human subjects protection training through the Collaborative Institutional Training Initiative (CITI) program. We further protect the confidentiality and privacy of participants using several data safety and protection safeguards of the study using REDCap which restricts data entry rights and access to team members with data management roles and responsibilities, logs all user activity, and builds an audit trail within the project.

